**Precis**

Uric acid (UA) is a terminal product of purine metabolism with strong antioxidant properties. UA has sizeable concentrations in biologic fluids only in humans and primates because they have a non-functional mutation of the enzyme uricase that, in other animals, transforms UA to allantoin. It has been hypothesized that this mutation has emerged evolutionarily because through this mechanism, humans can counteract the excessive oxidative stress that occurs in many critical pathologic conditions. Partially in contrast with this theory, high levels of UA have been associated with a number of negative health outcomes, including cardiovascular as well as all-cause mortality. Although it is possible that the UA elevation is merely a marker of critical health because it is an “inducible” antioxidant, researchers have questioned whether UA has beneficial or detrimental effect on health status. For example, we recently demonstrated that higher UA levels are cross-sectionally associated with higher levels of pro-inflammatory markers, and predict the increase in inflammatory markers over a 3-year follow-up. Understanding whether UA exerts a protective or detrimental effect on health is important in deciding whether mild hyperuricemia should or should not be aggressively treated.

Unfortunately, observational studies cannot fully address this question. In fact, we cannot exclude that the cross-sectional and longitudinal association between UA, inflammatory markers and negative health outcomes, may simply reflect the fact that UA is an inducible antioxidant that is produced in response to increasing oxidative stress. To verify the hypothesis that UA activates inflammation, we plan to conduct two complementary randomized controlled trials, each one including 10 treated and 10 control subjects. In the first trials, subjects with low UA will be administered 500 mg of UA intravenously. In the second trials, subjects with moderately elevated UA will be administered a single acute dose of Rasburicase. Then inflammatory markers will be measured at multiple points in time, for a total of 32 hours. We hypothesize that an acute increase in the circulating levels of UA will be followed by increasing levels of inflammatory markers. At the same time, an acute reduction of UA levels will be followed by a progressive reduction of inflammatory markers. This study should provide information that will help clinicians to decide whether to or not to treat mild hyperuricemia.

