
**Visit 2: history, physical exam and preliminary test**

Participants will arrive at NIA Clinical Research Unit after overnight fasting for 8 hours. A brief physical examination will be performed, including a sample of blood that will be collected for DNA extraction and characterization of the genes that indirectly or directly affect the UA metabolism. A physician will review subject’s eligibility criteria and immediately after the participant will be administered an MRI-spectroscopy that estimates the rate of phosphocreatinine resynthesis after exercise). Next, an Oral Lipid Tolerance Test (OLTT) will be performed. The OLTT consists of eating a standard fast-food type meal (with approximately 900 cal and 50 grams of fat), and measuring changes in lipids and inflammatory markers at 2 hour intervals for total of 8 hours. The meal will be prepared by a registered dietitian and will be consumed in no longer than 20 minutes. The inflammatory markers that will be sampled consist of IL-6, IL-6sr, TNF-α, TNF-r1, TNF-r2, sgp 130, and hsCRP (+Tryglycerides). However, based on the information available at the end of the study, some of these inflammatory markers may not be measured and may be substituted with markers without changing the quantity of blood collected. OLTT will start in the morning after 8 hours of fasting. After the meal, subjects will not eat for the next 8 hours but will have free access to water and ice. After 8 hours a standard meal will be available. Blood samples will be drawn before the meal and every 2 hours after the first bite of the meal over an 8-hour period. The total amount of blood needed for the tests/assays included in the OLTT will be 40 mL including a 1mL waste at each time point. The blood will be sent via courier to NIA Lab at the 2 hour intervals. From there the blood will be sent to the respective labs for processing. After discharge, the patient will be given instruction for the following visit. In particular, participants will be advised to drink 8 8oz glasses of water on the day before the visit and at least 2 further glasses in the morning before the infusion.

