Total and differential white and red blood counts, hemoglobin, hematocrit, platelets, glucose, BUN, creatinine, Uric Acid, LDH, CPK, electrolytes, AST, ALT, ALP, albumin, globulin, bilirubin (total and direct), haptoglobin, HDL and total cholesterol, triglycerides, and CRP will be drawn at the 24 hour timepoint to make sure that there has been no change post intervention. The total amount of blood needed for this will be 15 mL.

*11. Urine collection*

A urine sample will be collected at baseline (first morning void on Day 1), every void between 1 and 12 hours after infusion and 24 hours after infusion. The urine samples will be used to evaluate uric acid levels in the urine and potentially markers of oxidative stress damage.

*12. MRI muscle spectroscopy.*

Magnetic resonance spectroscopy (MRS) will be used to study energy metabolism in muscle during and after exercise. As already mentioned, MRS is performed once on Visit 2 and a second time 24 hours after the infusion of the study drug, immediately before performing the second Lipid Tolerance Test. Participants will be carefully screened for MRI contraindications before performing the tests. Also, they will be given a choice of receiving the MRI. Participants with contraindication to MRI or refusing MRI will not receive MRI but will be still enrolled in the other parts of the study, without any effects on their compensation.

*13. Lipid Tolerance Test*

24 hours after the injection, A second OLTT will be performed using exactly the same protocol used in Visit 2.

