**6. RISKS/DISCOMFORTS**

Risk associated with the administration of UA solution: UA is a physiological constituent of cells and blood in humans. Based on published studies, I.V. administration of UA 1,000 mg and 500 mg in 250 ml of 0.1% lithium carbonate/ 4% dextrose solution over a 60 minute period was not associated with any adverse event, change in blood pH, clinical, hemodynamic and biochemical parameters. In a total of 44 persons, the administration of UA 500 mg was associated with an average increase of circulating levels between 3 and 4 mg/dL which creates a transitory increase of the UA concentration. The transitory increase of the UA concentration did not cause any risk, while it was associated with increased plasma antioxidant activity, reduced oxidative stress marker and better endothelial function. There is a very low risk that UA may precipitate in renal tubules and cause kidney damage. This risk is minimized by administering a dose of UA that should not increase the UA concentration above the solubility threshold, checking the urine specific gravity is below 1015 before the administration, ensuring abundant intake of water, inducing a mild urine alkalinitation (by administering orally sodium bicarbonate) and monitoring the urine pH and specific gravity.

Risk associated with the administration of Rasburicase: Potential side effects are listed in the table below. These side effects have been observed in 703 patients affected from leukemia, lymphoma, and solid tumor malignancies who are receiving anti-cancer therapy. The most severe side effects of Rasburicase administration are hypersensitivity reactions including anaphylaxis (<1%), and methemoglobinemia (<1%).

| **Serious Adverse Reaction** | Percentage (%) of Subjects (total n=703) |
| --- | --- |
| Allergic reactions including anaphylaxis | <1 |
| Rash | <1 |
| Hemolysis | <1 |
| Methemoglobinemia | <1 |
| Fever | 5 |
| Neutropenia with fever | 4 |
| Respiratory distress | 3 |
| Sepsis | 3 |
| Neutropenia | 2 |
| Mucositis | 2 |
| **Adverse Reaction** | Percentage (%) of Subjects (total n=436) |
| Vomiting | 50 |
| Fever | 46 |
| Nausea | 27 |
| Headache | 26 |
| Diarrhea | 20 |
| Mucositis | 15 |
| Rash | 13 |

Note: an antibody response to a single dose of rasburicase (immunogenicity) has also been observed. To the date of this protocol, the immunogenicity issue is not applicable to our study since the drug is not approved for the treatment of adults.

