These sample size procedure specification is based on previous findings from Waring and our group. Waring et al. showed that infusions of 1,000 mg and 500 mg of UA were associated with an increase of UA circulating levels of 3.2-4.9 mg/dL with this increase persisting for 10-12 hours. For the purpose of the power analysis, we assumed a very conservative increase in UA of 2.5-3 mg/dL persisting from 2 to 12 hours, and a progressive decline in UA levels after 2 hours returning to baseline by 48 hours. The control group was assumed to show no systematic change in UA (16,18, 19). Further, the report by Ruggiero et al found that IL6 increased by 0.08 per mg/dL increase of uric acid. We examined an associated increase of 0.04, 0.06 and 0.08 pg/ml for each mg/dL change in UA. Using these relationships, IL-6 was sampled at each point in time from a normal distribution with a standard deviation as found in Ruggiero et al. of 0.02 for a sample size of 976 subjects (21). The resulting IL-6 was entered into a mixed effects model being regressed on time and group with subject as a random effect. This model was compared to a model including group using a log-likelihood test, and the null was accepted at p> 0.05. The simulation was repeated 100 times to determine the number of times the null hypothesis was rejected. For 10 subjects per group, with a rise in UA of 2.7 mg/dL, a coefficient of 0.04 gave a power of 0.94, a coefficient of 0.06 gave a power of 0.98, and a coefficient of 0.08 gave a power of 1.00. For rasburicase, we postulated that UA would go to zero. With the current model, UA increase of 2.0 with progressive decrease over time gives power of 0.92, 0.93, 0.93 for the coefficients of 0.04, 0.06 and 0.08. UA increase of 1.5 had a power in the 0.6-0.7 range for the 3 coefficients.

With this assumption, 10 subjects per group resulted in a power of 0.97 for a coefficient of 0.04, 1.00 for a coefficient of 0.06, and 1.00 for a coefficient of 0.08.

Enrollment: a total of 40 participants will be enrolled. According to inclusion/exclusion criteria 20 participants, 10 men and 10 women, will be recruited in Trial A: Uric Acid versus placebo trial and 20 participants, 10 men and 10 women, in Trial B: Rasburicase versus placebo trial. To maintain the number of participants as above, we will screen 6 more subjects, (3 men and 3 women for each cohort), that will be enrolled only if some drop-outs occur.

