**14. PHARMACEUTICAL INFORMATION**

**Uric Acid**

Description: UA I.V. solution is manufactured by Florida Biologix, Center of Excellence for Regenerative Health Biotechnology, University of Florida, USA (see ***Appendix A***). The description of UA chemistry and physiology in humans is reported in ***Appendix B***.

Dose: UA 500 mg in 250 ml of 0.1% lithium carbonate/4% dextrose solution will be administered intravenously over a 60 minute period. Before administration and on the same day, UA solution will be filtered for both UA microcrystals using a 0.22 mm Millex filter (Millipore, Molsheim, France), and for virus using the Millipore Viresolve NFR  (OptiScale-25 Small Volume Disposable Capsule Filter). The Millipore in-line filter will be done generating the required 20-50 psi of pressure for fluid passage that will be created using a peristaltic pump. The vehicle was selected because it allows stable dissolution of UA and theoretically should not affect serum antioxidant capacity.

Route of Administration: intravenous administration of reconstituted formula.

Clinical pharmacology: UA was administered intravenously in two previous clinical studies conducted at the Clinical Pharmacology Unit and research Center, The University of Edinburgh, UK. Infusion of 1,000 mg of UA in a 500 ml 4% dextrose/0.1% lithium carbonate vehicle led to a time-dependent UA increment of about 3.2-4.9 mg/dL. Serum UA concentration exhibited a two-component decay with a mean elimination half-life of 10.8 h. The elimination and distribution phase after infusion of 1,000 mg of UA has been previously described (16).

Drug Interactions: no data are available.

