Toxicities: UA is a physiological constituent of the cell cytosol and a byproduct of nucleotide metabolism in humans. Biochemical evidence suggests that UA is a Reactive Oxygen Species scavenger (44-46). Phase 1 studies of UA infusion have been performed in 52 subjects. In the first study, 8 healthy non-smokers aged 24±2years were administered with a UA 1,000 mg in 250 ml of 0.1% lithium carbonate/ 4% dextrose I.V. solution over a 60 minute period. In the second study, 20 community healthy persons aged 23±3years were treated with a UA 500 mg in 250 ml of 0.1% lithium carbonate/ 4% dextrose I.V. solution over a 60 minute period. In the third study, 8 adult smokers (30 yrs), 8 adults affected from Type 1 diabetes (30 yrs) and 8 adult controls (30 yrs) were infused with UA 1,000 mg in 500 ml of 0.1% lithium carbonate/ 4% dextrose over a 60 minute period. No severe adverse events, adverse events nor change in clinic, hemodynamic and biochemical parameters have been reported in these studies (16,17,18,19).

Storage: UA solution will be securely stored in the NIA Research Pharmacy, and under the appropriate conditions. Stability tests will be performed by Florida Biologix at 5 times points over an 18 month period (3, 6, 9, 12 and 18 months).

Mechanism of Drug Accountability: All dispensing of UA and any destruction of the chemical doses will be documented on a protocol specific Investigational Agent Accountability Record, maintained in the NIA Research Pharmacy.

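### Trial A's lipid-test limb of the primary aim runs at 24-32 h, when the stated 10.8 h half-life leaves about 23% falling to 14% of the UA rise; UA is not measured after the start of the test, and the inputs for the rise conflict

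*Protocol*

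**What the plan says.** Protocol Section 2 (Objectives), repeated in Section 9, gives the primary aim two limbs. One is the concentration of inflammatory markers after UA is raised or lowered. The other is whether the UA level changes the inflammatory response to a lipid tolerance test.

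- **Timing of the test.** Section 5, Visit 3, item 13: "24 hours after the injection, A second OLTT will be performed using exactly the same protocol used in Visit 2". The Visit 2 procedure it refers to is: "Blood samples will be drawn before the meal and every 2 hours after the first bite of the meal over an 8-hour period". The Precis agrees: "inflammatory markers will be measured at multiple points in time, for a total of 32 hours".
- **UA sampling.** Section 5, Visit 3, item 9 lists baseline, 1, 2, 4, 8, 12 and 24 h, and then two weeks.
- **Decay.** Section 14, Uric Acid, Clinical pharmacology: "Serum UA concentration exhibited a two-component decay with a mean elimination half-life of 10.8 h".
- **Planning profile.** Section 11: "we assumed a very conservative increase in UA of 2.5-3 mg/dL persisting from 2 to 12 hours". The same sentence has the level declining from 2 h and back at baseline by 48 h. Section 11 also says that the rise seen in earlier studies lasted 10-12 h.
- **Size of the rise.** Section 11 gives 3.2-4.9 mg/dL for 1,000 mg and 500 mg together. Section 14 says that 1,000 mg "led to a time-dependent UA increment of about 3.2-4.9 mg/dL". Section 6, citing 44 people: "administration of UA 500 mg was associated with an average increase of circulating levels between 3 and 4 mg/dL".
- **Dose in the third earlier study** (smokers, type 1 diabetics and controls). Section 1 says 500 mg. Section 14, Toxicities, says: "8 adult controls (30 yrs) were infused with UA 1,000 mg in 500 ml".

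**The concern.** The second limb asks what a different UA level does to the response to a fatty meal. That requires the treated and placebo groups to differ in UA while the meal is being handled. In Trial A the meal is given at least 12 h after the end of the 10-12 h for which Section 11 says the rise lasts, and more than two half-lives after the infusion ends. The contrast being tested is then a fraction of the one achieved. UA is not sampled after the start of the test, so its course during the test is unobserved.

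A Trial A lipid test showing no difference could mean that UA has no effect, or that UA was no longer much raised. Section 11 gives no power for this limb. The profile and rise used for the power that it does give cannot be squared with the other sections.

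**Working it through.** **1. The plan's own figure.** Section 11 states power of 0.94 for 10 per group, a 2.7 mg/dL rise, an IL-6 coefficient of 0.04 pg/mL per mg/dL, SD 0.02 and a likelihood-ratio test at 0.05. In a balanced random-intercept model the treatment term reduces to a comparison of subject means, so it was simulated that way (4,000 trials). Profiles tried were linear decline, plateau to 12 h and 10.8 h exponential.

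- SD 0.02: power 1.00 for every profile, time grid and coefficient.
- If 0.02 is really a standard error from the 976 people cited, SD = 0.02 × √976 = 0.62, and power is about 0.10-0.39 across the three coefficients.

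Neither reproduces 0.94. Section 11 says that assay variation entered through the variability of the UA change, but gives no value. Power in the lipid-test window alone (2.7 mg/dL, 10.8 h decay) is about 1.00 with SD 0.02 and about 0.07-0.08 with SD 0.62. The SD is a separate question that swamps the effect of timing, so the size of this point is given in UA, not in power.

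**2. The window.** Start 24 h, sampling at 0, 2, 4, 6 and 8 h: 24 to 24 + 8 = 32 h, as in the Precis.

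**3. Rise left under the stated half-life.** Assume that the increment over baseline decays with a single 10.8 h half-life from the end of the 60-minute infusion (1 h). Fraction left = 2^(−(t − 1)/10.8).

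| t | Fraction | From a 3-4 mg/dL peak | From 2.7 mg/dL |
|---|---|---|---|
| 24 h | 2^(−23/10.8) = 0.229 | 0.69-0.91 | 0.62 |
| 32 h | 2^(−31/10.8) = 0.137 | 0.41-0.55 | 0.37 |

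The mean over the five sampling times is 18%. Starting the decay at 0 h gives 21.4% and 12.8%; starting it at 2 h gives 24.4% and 14.6%. A faster first component, as the two-component description implies, would leave no more than this.

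**4. Rise left under the planning profile.** Section 11 can be read as a linear decline from 2 h to 48 h, (48 − t)/46, or as flat to 12 h and then linear, (48 − t)/36.

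| t | Linear from 2 h | Flat to 12 h | mg/dL from 2.7 |
|---|---|---|---|
| 24 h | 24/46 = 52% | 24/36 = 67% | 1.4-1.8 |
| 32 h | 16/46 = 35% | 16/36 = 44% | 0.9-1.2 |

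The planning profile therefore leaves about 2.3 times (0.52/0.229) to 3.2 times (0.444/0.137) what the half-life leaves.

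**5. Who received which dose.** Section 14, Toxicities, lists 8 people at 1,000 mg, 20 at 500 mg and 8 + 8 + 8 = 24 at 1,000 mg. The total of 8 + 20 + 24 = 52 matches its stated 52. At 500 mg that is 20 people. The 44 in Section 6 is 20 + 24, which requires the third study to be at 500 mg, as in Section 1. Sections 1 and 6 fit each other; Section 14 does not fit them.

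**The case against.** **The timing has reasons.** The repeat test has to match Visit 2, in the morning after an 8-hour fast. A high-fat meal on Day 1 would disturb the serial markers after infusion. An effect acting through gene transcription could also outlast the UA peak. This stands: it explains the choice and is why the limb is weakened rather than lost. It does not restore the exposure.

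**A reader might infer that the groups hardly differ in UA by then.** The documents do not support that. Section 11's own profile leaves 0.9-1.8 mg/dL over 24-32 h. The half-life comes from 1,000 mg, given in the study listed in Section 14 to volunteers of mean age 24, and it may differ at ages 50-75. UA is sampled at 24 h, which the visit schedule names as the baseline for the second lipid test, so the contrast at the start will be known.

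**A reader might infer that the assumed 2.5-3 mg/dL is too high.** If 3.2-4.9 mg/dL belonged to 1,000 mg alone and the rise were proportional to dose, 500 mg would give 1.6-2.45 mg/dL. Proportionality is an assumption, and Section 6 directly reports 3-4 mg/dL for 500 mg, which would make 2.5-3 cautious. Section 14's pharmacology text is silent on the rise at 500 mg.

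**A reader might take the stated power of 0.6-0.7 at 1.5 mg/dL as the power of the lipid test.** It belongs to the serial IL-6 model, and the same paragraph gives 0.92-0.93 at 2.0 mg/dL. It says nothing about the lipid test.

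**A reader might infer that the plan will count a Trial A null against UA.** Nothing says so. Section 11 says only that the course of UA will be evaluated and outcomes compared. The fault is that this limb has primary status with no qualification.

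**Conclusion.** The point holds for Trial A. The lipid-test limb is tested when about 23% falling to 14% of the rise remains under the protocol's own half-life, or 52-67% falling to 35-44% under its own planning profile. These differ by a factor of two to three, and no UA sample during the test will show which is nearer the truth. The first range rests on single-exponential decay from the end of infusion and on a half-life carried over from 1,000 mg. The second rests on a linear return to baseline.

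Sections 1, 6, 11 and 14 do not agree on which dose gave which rise in how many people. That leaves the claim of a conservative rise unverified, not disproved. Trial B's lipid test is not touched by this point.

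**What to change.** 1. Assay UA on the serum banked at each post-infusion lipid-test time point in Trial A, and report the between-group UA difference over 24-32 h. The blood-collection schema already sets aside 1 mL of serum at each point. The 24 h sample covers the start, so this adds 26, 28, 30 and 32 h: 4 × 20 participants = 80 assays, with no new visit or blood draw. The laboratory should confirm that the volume suffices.
2. State in Sections 2, 9 and 11 that the Trial A lipid test is a supportive test at reduced exposure, and that a null result there is not evidence against a UA effect. Keep the serial IL-6 response, at all scheduled times including 24 h, as the test the trial is sized on.
3. Reconcile Sections 1, 6, 11 and 14 on dose, rise and number of people, and the decay in Section 11 with that in Section 14.
4. Rerun and restate the Trial A power with the reconciled 500 mg rise and the 10.8 h decay, giving every variance input.

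The cost is the assays, one simulation and some wording. The real downside is that Trial A claims less from its lipid test.

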**Visit 4: 2 weeks post-intervention**

A follow-up visit will be scheduled two weeks after treatment. This visit is mostly for checking that all physiological parameters return to the baseline levels and there are no side effects. Blood samples will be collected at the NIA Clinical Research Unit in the morning after 8 hours overnight fasting and used to measure: complete CBC with differential count, glucose, BUN, creatinine, UA, LDH, CPK, electrolytes (Na+, K+, Cl-; Ca++, Mg+), AST, ALT, ALP, albumin, globulin, bilirubin (total and direct), haptoglobin, HDL-LDL and Total cholesterol, triglycerides, and CRP will be estimated from blood samples. An EKG will be obtained. In addition, samples will be obtained to measure inflammatory markers, circulating antioxidants, markers of oxidative damage and RNA expression (see point 5-8 above for full details).

The total amount of blood drawn on this visit is 49 mL. An additional visit may be scheduled at 4 weeks from intervention for participants whose UA levels are not back to the baseline levels.

